### Data management

All data will be collected electronically using an online survey tool which provides a secure survey website (SSL encryption). Password protected data files will be utilised for participant tracking during the study and data analyses. Access to the study data will be restricted to the research team. Data will be securely stored for a period of 7 years after the completion of the study. Backup of electronic data will be performed regularly and stored securely on a password protected internal network.

### Statistical methods

A range of descriptive and multivariate data analyses will be used to assess the aims of the study. Descriptive statistics (e.g., Chi-square for categorical variables; means and standard deviations for continuous variables) will be presented for the sample demographics, number of times participants access the program, and proportion of participants completing the program. Demographic characteristics of the sample will be compared to country-wide averages obtained from the most recent Australian Census data. Characteristics of infants taking part in the research will be compared to MCH data for babies born within the same geographic area at the time of study recruitment. A mixed-design analysis of variance (split-plot ANOVA) will be conducted to compare the intervention conditions (between-subjects factor) on each of the continuous outcomes at follow-up (within-subjects factor). Effect sizes will be reported where appropriate, with 0.01, 0.06 and 0.14 as small, medium and large effect sizes for multivariate η2, while 0.2, 0.5 and 0.8 are small, medium, and large effect sizes for Cohen’s *d*. All analyses will control for child age given that time of enrolment varied between 2 and 12 weeks postpartum. Finally, intention-to-treat analysis will be conducted using Full Information Maximum Likelihood for missing follow-up data.

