### Study objectives

Our objectives are to examine:whether randomisation of participants to a condition that receives additional email prompts that encourage parents to log in to the program, will result in greater use of program strategies (primary outcome) as well as greater retention to the research at follow-up (at 4 months of infant age)whether parents who have the program recommended by their MCH nurse are more likely to engage with the program (as measured by program completion rates), than those who are recruited via an online advertisement for the program; and, whether they are also more likely to use the suggested strategiesthe demographic profile of parents who choose to take part in the online program with a view to identify any over- or under-representation of parents (compared to Australian Census data where possible) based on: household income, socioeconomic status, education, language spoken and support available to parents; or child characteristics, including birth order of infant, infant age, gender, birth weight, gestation, and where the baby sleeps at night; and, to see how this differs for participants who are recruited via a popular parenting website compared to those recruited via their MCH nursethe psychosocial well being of participants (specifically depression symptoms, fatigue and cognitions surrounding infant sleep in parents, and in infants, night waking behaviour, and, sleep, crying or feeding problems), with a view to identify any specific concerns that may be addressed in the development of new online programs for parents of infants

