### Study setting and recruitment

Participants will be primary carers of infants aged 2 to 12 weeks, recruited by one of two recruitment modalities: advertising on the Raising Children Network (www.raisingchildren.net.au), or recommendation from their MCH nurse. The Raising Children Network website is a non-commercial, evidence-based, quality assured, government-funded online resource that covers a broad range of parenting topics and had over 5.7 million visits in the 2013 calendar year (personal communication). A notice will be placed on relevant pages on the Raising Children Network, as well as its social media (e.g., Facebook, Twitter). This notice will contain a link to the study website where parents can gain more information and take part in the program if desired.

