Recruiting some of our sample from Australian wide online advertising and some from a specific region, introduces systematic differences to the groups. In an attempt to reduce this as much as possible, we selected the Melbourne (state of Victoria, Australia) Local Government Area (LGA) of the City of Yarra for MCH nurse recruitment, due to both its high birth rate per annum [45], and broad cultural and socioeconomic diversity [46]. All MCH nurses within this LGA (11) will invite parents of infants attending the 2 week appointment to participate in the trial. The 2 week appointment will be specifically targeted as it was suggested by the nurses that this appointment is less intensive than the in-home appointment at 7–10 days postpartum, and it is unusual for parents of infants aged less than 2 weeks to request information on infant sleep and crying so soon after birth. Recruitment will run for a 12 week period and will allow for later determination of the percentage of parents in the general community that are likely to take part in an online program if suggested by their MCH nurse (birth rate data for this region, throughout this time period will be compared to our sample). MCH nurses will provide parents with a postcard, inviting them to participate in the program. The postcard will contain brief information about the study and a link to the study website so they can gain further information about the research. Participants who indicate that they heard about the Cry Baby program via their nurse *and* via online advertising will be classified as having been recruited via their nurse since it is the effect of encouragement from a health professional that we aim to examine. The Cry Baby program is currently only available to those willing to take part in the research trial and has not been broadly advertised outside the Raising Children Network. This means it is very unlikely that parents would have the program suggested to them by other health professionals.

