#### Baseline questionnaire

The participant will be asked to complete a baseline questionnaire online. This will collect demographic information about the parent (age, gender, educational attainment, employment status, country of birth, main language spoken at home, and household income) and infant (birth order, date of birth, gender, birth weight, gestation, and where the baby sleeps at night). Area-level socioeconomic disadvantage will be determined using the *Socio-economic Indexes for Areas* [46] based on participant postal code and population census data.

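### Objective 3 uses one benchmark per characteristic for a sample from two catchments, so residence can be read as over- or under-representation

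*Protocol article*

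**What the plan says.** The protocol's Study objectives section describes the third objective as a demographic profile "with a view to identify any over- or under-representation of parents (compared to Australian Census data where possible"), and adds that the profile will be contrasted between website and nurse recruits.

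Under Study setting and recruitment, participants are "recruited by one of two recruitment modalities: advertising on the Raising Children Network" or recommendation by a nurse. The nurse route is confined to one council: the authors chose the "Local Government Area (LGA) of the City of Yarra for MCH nurse recruitment". They acknowledge the consequence: "Recruiting some of our sample from Australian wide online advertising and some from a specific region, introduces systematic differences to the groups". Their stated mitigation is that Yarra has a high birth rate and a diverse population. Local data enter that section once, for estimating nurse uptake: "birth rate data for this region, throughout this time period will be compared to our sample".

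The Statistical methods section fixes two benchmarks. For parents: "Demographic characteristics of the sample will be compared to country-wide averages obtained from the most recent Australian Census data". For infants, their characteristics "will be compared to MCH data for babies born within the same geographic area"; the area is not named. The Baseline questionnaire section assigns area-level disadvantage "based on participant postal code and population census data".

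**The concern.** A comparison with an outside population shows who chooses to take part only if that population is the one from which participants could have come. Here the parent benchmark is national while one stream can arise only in a single council. The infant benchmark comes from a service that the Background describes for Victoria, while the other stream can arise anywhere in Australia.

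The Background expects online programs to attract better-educated parents of higher socioeconomic status, and it presents encouragement by health professionals as one way to correct this. The profile by recruitment route is the evidence that objective 3 would supply on that idea. If Yarra differs from Australia in income, education or language, nurse recruits can look unrepresentative, or different from website recruits, for reasons unrelated to who accepts a nurse's invitation. The postcode-based disadvantage index is the clearest case, because it describes where a participant lives.

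**Working it through.** The documents give no local or national shares and no expected split between streams, so there is no figure of the plan's own to reproduce. The check has two parts.

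**1. Matching catchments to benchmarks**

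| Stream (catchment) | Parents against country-wide Census | Infants against MCH data |
|---|---|---|
| Website (Australia) | matched | mismatched if the area means Yarra or Victoria |
| Nurse (City of Yarra) | mismatched | matched with City of Yarra data |

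Two cells are sound. One is mismatched as written, and one depends on an undefined term. If the area were meant to be each infant's own, website infants outside Victoria would need MCH data that the document does not describe.

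**2. Size, by illustration only**

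From the document: recruitment target N = 152 (Sample size and condition allocation).

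Assumed: national share pN = 30%; nurse share of the sample w; Yarra-national gap D; no self-selection, so each stream mirrors its own catchment.

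- Expected pooled share = pN + w × D, so the false excess is w × D.
- Standard error at N = 152: √(0.30 × 0.70 / 152) = 3.7 points.
- Smallest case, w = 15%, D = 10: 0.15 × 10 = 1.5 points, and 1.5 / 3.7 = 0.4 standard errors.
- Largest case, w = 50%, D = 30: 0.50 × 30 = 15 points, and 15 / 3.72 = 4.0 standard errors.
- Nurse stream alone, w = 100%: the whole gap appears. With an assumed 30 nurse recruits the standard error is √(0.30 × 0.70 / 30) = 8.4 points, so gaps of 10 to 30 points are 1.2 to 3.6 standard errors.

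The table gives the chance that a two-sided 5% one-sample normal test against pN flags the pooled sample of 152. The test uses the null standard error √(pN(1 − pN)/N), and the sampling variance is [w·pL(1 − pL) + (1 − w)·pN(1 − pN)]/N with pL = pN + D.

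| Gap D | w = 25% | w = 50% | w = 75% |
|---|---|---|---|
| 5 points | 7% | 11% | 18% |
| 10 points | 11% | 28% | 52% |
| 20 points | 27% | 76% | 97% |

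With a small gap and a small nurse share, the rate is close to the nominal 5%. With a gap of 20 points and half the sample from nurses, a 10-point false excess would be flagged about three times in four.

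The raw nurse-versus-website difference carries the full gap D whatever w is. With 30 nurse and 122 website recruits its standard error is √(0.21/30 + 0.21/122) = 9.3 points, a 95% half-width of 1.96 × 9.3 = 18 points. Treating benchmarks as fixed, subtracting them removes the geographic gap but does not make this interval narrower.

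**The case against.** The authors disclose the geographic difference and chose a diverse council to reduce it. Objective 3 already splits the profile by recruitment route and limits the Census comparison to where it is possible. The article's short wording does not exclude tables by stream. The national benchmark answers a question the objectives state: how participants compare with the Australian population. The infant sentence may have been meant only for nurse-stream infants. The objective is descriptive, and the size shown above is assumed.

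Much of this stands. The national comparison is legitimate and should stay. The infant part is an ambiguity, not a demonstrated error. What does not stand is that disclosure or the split by route resolves the problem. Diversity within a council does not make its averages equal to the country's, and two raw profiles from different places still differ by place. The local birth data serve only the uptake percentage.

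A reader might go further and infer that the choice of council will create the over-representation and the difference between streams. The documents do not support that, because they give no Yarra or national share for any characteristic and the gap could be small. Nor do they show how many values the disadvantage index can take among nurse recruits; one can say only that it mainly reflects the area chosen.

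**Conclusion.** The concern holds in a limited form. Nurse-stream parents are set against a population they were not drawn from, and so are website infants if the unnamed area is Yarra or Victoria. In those comparisons residence and self-selection cannot be told apart, and the nurse-versus-website profile carries the same geographic difference. It would be wrong to infer that all the benchmark comparisons fail: website parents against national figures, and nurse-stream infants against local MCH data, are properly matched.

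The mismatch follows from the text; its effect does not. Under the assumed values the effect runs from negligible to about four standard errors, driven by the nurse share and the Yarra-national gap. It bears on the interpretation of descriptive objective 3 and leaves the randomised comparison of email prompts untouched. It is worth correcting because it concerns a stated benchmark and the remedy is cheap.

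**What to change.** In the Statistical methods section:

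- Report the benchmark comparison separately for each recruitment stream. For nurse-stream parents, add City of Yarra Census figures beside the national ones. Keep the national comparison, since the objectives call for it.
- State which area the infant comparison refers to, and restrict the MCH comparison to infants from that area. For website infants, use national birth data only for variables where such data exist; the documents do not show that they cover, for example, where the baby sleeps.
- Read the nurse-versus-website profile alongside each stream's difference from its own catchment, and state the limited precision if the nurse stream is small.

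The cost is some extra public tables and slightly more descriptive analysis. Postcode is already collected, so nothing further is needed from participants.

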### Eligibility criteria

Participants will provide informed consent online (by selecting a checkbox that appears after the Information Statement and before the baseline questionnaire), before any study procedures occur. All parents of newborn infants aged less than 12 weeks, who access www.raisingchildren.net.au or who are seen by their MCH nurse at their 2 week check in the City of Yarra will be invited to participate in the study. However, parents will be excluded from the study if they are under the age of 18 years, have a child over the age of 12 weeks at the time of enrolment into the study, have insufficient English comprehension to complete the questionnaires, have an infant born before 33 weeks gestation, or if the parent and/or infant suffer from a serious medical condition.

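### Objective 3 compares a sample restricted by eligibility with reference data that carry no stated matching restriction, so part of any gap on home language, gestation or birth weight reflects entry criteria and not uptake

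*Protocol article*

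**What the plan says.** Study objectives (third objective) describes the profile of parents who take part "with a view to identify any over- or under-representation of parents (compared to Australian Census data where possible) based on: household income". The list continues with "education, language spoken and support available to parents", and for infants with "birth order of infant, infant age, gender, birth weight, gestation". The same objective also compares website recruits with nurse recruits.

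Statistical methods names the references. For parents: "Demographic characteristics of the sample will be compared to country-wide averages obtained from the most recent Australian Census data". For infants: "Characteristics of infants taking part in the research will be compared to MCH data for babies born within the same geographic area", taken at the time of recruitment. No restriction by gestation, health, parental age or English ability is stated for either.

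Eligibility criteria excludes parents who "have insufficient English comprehension to complete the questionnaires, have an infant born before 33 weeks gestation", as well as parents under 18, infants over 12 weeks, and families in which parent or infant has a serious medical condition. The Baseline questionnaire section records the main language used at home, not ability in English.

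**The concern.** A comparison meant to show who chooses an online program needs a reference made up of people who could have chosen it. Here some of the characteristics being compared are also entry criteria, or are closely tied to them. The sample will then differ from the reference even if every eligible family is equally likely to join. A correctly located reference area would not remove this.

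What is at stake is how the reach results are read. The Abstract asks whether the parents who would benefit most are among the users, and the Background names prematurity as a risk factor for abusive head trauma. According to Study setting and recruitment, the program is at present open only to trial participants, so trial eligibility is also the gate to access. A shortfall of very preterm infants, or of families who speak another language at home, could be taken as low uptake when some of those families were not allowed to enrol.

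**Working it through.** The plan gives no figure for this comparison, so there is none to reproduce. The only figure borrowed from it is the recruitment target of 152 (Sample size and condition allocation), which was set for the randomised comparison. All population shares below are assumptions. Throughout, eligible families are taken to be equally likely to join, so any gap comes from eligibility alone.

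**Gestation.** Let f be the share of births before 33 weeks. The reference contains f and the sample contains exactly 0.
- Expected number among 152 without the exclusion: 152 × f. For f = 1.5% this is 2.3 infants, and for f = 2% it is 3.0. Over a wider range, f = 0.5% to 3%, it is 0.8 to 4.6.
- Chance of seeing none among 152 without the exclusion: (1 − f)^152, which is 0.10 at f = 1.5% and 0.05 at f = 2%.

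**Low birth weight.** Assume 6.5% of births are low birth weight and that nearly all births before 33 weeks are among them. Eligible share = (6.5 − f)/(100 − f).
- f = 1.5: 5.0/98.5 = 5.08%, a gap of 1.4 points.
- f = 2: 4.5/98 = 4.59%, a gap of 1.9 points.
- In 152 infants: 152 × 0.065 = 9.9 expected, against 7.7 and 7.0, so 2 to 3 infants.

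**Mean birth weight.** If infants born before 33 weeks weigh 1,500 to 2,000 g less on average than eligible infants, the reference mean lies lower by f × gap. With f = 0.5% to 3% this is about 8 to 60 g. The standard error at 152, with an assumed SD of 550 g, is 550/√152 = 45 g.

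**Main language at home.** Assume 20% use another language at home, and that x = 2% to 4% of all adults lack the English needed, all of them within that 20%. Eligible share = (20 − x)/(100 − x).
- x = 2: 18/98 = 18.4%, a gap of 1.6 points.
- x = 4: 16/96 = 16.7%, a gap of 3.3 points.
- In 152 parents: 152 × 0.20 = 30.4 expected, against 27.9 and 25.3, so about 2 to 5 parents.
- On a wider grid (10% to 30% using another language, 5% to 30% of those excluded) the gap is 0.5 to 6.9 points.

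**Against sampling error.** The 95% margins at 152 are 1.96 × √(0.065 × 0.935/152) = 3.9 points for low birth weight and 1.96 × √(0.20 × 0.80/152) = 6.4 points for language. If a two-sided 5% one-sample test were applied, it would flag the built-in gap in about 8% to 12% of trials for low birth weight and 7% to 16% for language, against a nominal 5%. At the far corner of the wider language grid (30% and 30%) the figure is 46%.

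Serious medical conditions and parental age under 18 are not quantified. The infant reference is local, so if only nurse-recruited infants are compared with it, the infant counts shrink in proportion. The percentage-point gaps do not change.

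**The case against.** The strongest reply is that this is a descriptive benchmark in a condensed article. Study objectives limits the Census comparison to what is possible, Statistical methods sets no hypothesis or decision rule for it, and filters on reference data are often left to a fuller plan. The exclusions are openly stated, nothing says that a gap will be put down to refusal, and parents complete the eligibility questions online, so exclusion counts may already be planned. The Background's reach concern centres on income, place of residence, education and socioeconomic status, none of which is an entry criterion.

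Most of this bears on size and weight, and it stands. It does not remove the mismatch: the references are named, and as named they do not match the people who could enrol.

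Some stronger readings are tempting and should be resisted.
- A reader might infer that non-English-speaking families as a whole are turned away. The criterion is that parents "have insufficient English comprehension to complete the questionnaires", so families who use another language at home but read enough English remain eligible.
- A reader might quote the low-birth-weight gap as a relative shortfall of 22% to 29% (1.4/6.5 to 1.9/6.5). Birth weight is not an exclusion criterion, the inputs are assumed, and in counts this is 2 to 3 infants.
- A reader might conclude that infant age should be dropped. The entry window does make age uninformative against an outside population, but age remains a valid descriptor for website versus nurse recruits, and the Intervention section uses it to learn when the program is most useful.

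**Conclusion.** The point holds in a limited form. Carried out as written, the external comparison mixes eligibility with uptake on three characteristics: gestation (complete below 33 weeks), main language at home (partial) and birth weight (indirect and probably small). The direction follows from the entry criteria for gestation, and for language as long as some parents who use another language at home fail the comprehension criterion. That the references are unrestricted is read from their description and from the absence of any stated limit.

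The size cannot be derived from the documents. On the assumed shares it is about 1.4 to 1.9 points for low birth weight and 1.6 to 3.3 points for language, or roughly 2 to 5 families of 152, which is inside the sampling margin. It deserves correction because it bears on a stated objective and is cheap to put right. A reader might go further and suppose that the trial's main result is compromised. It is not: the primary outcome and the randomised comparison do not use these references.

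**What to change.** In Statistical methods:
- Restrict the MCH reference to infants born at 33 weeks or later and, if recorded, to parents aged 18 or over.
- Use Census tables by English proficiency where they are available. The documents do not show whether they are, and proficiency would only approximate the comprehension criterion.
- Where a reference cannot be restricted, state that gaps on language, gestation and birth weight partly reflect eligibility, and that reach among excluded groups cannot be estimated.
- Report the numbers excluded at online screening, by reason, beside the comparison if they are recorded.
- Keep infant age for the website versus nurse comparison, but do not interpret it against an external population.

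The cost is a little extra data handling and a narrower conclusion. No further data are needed from participants. If neither reference can be filtered, the limiting sentence alone is enough.
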